### Sample size considerations

Sample size calculations were conducted accounting for the clustered design [16]. Throughout we have assumed a harmonic mean of 145 TB patients/cluster, nine clusters per arm and a two-sided type I error of 5%.

Proportion with >80% adherence: Assuming a percentage with non-adherence in the standard of care arm of 30% and coefficient of variation of variation of 0.12, we will have 90% power to detect a 40% reduction in the endpoint in the intervention arm. For a successful outcome at the end of treatment of 80% in the standard of care arm and a coefficient of variation of 0.06, we will have 90% power to detect an increase to 90%. For unfavourable outcome 18 months after enrolment (defined as on-treatment lost to follow-up, death, treatment failure, and recurrence) of between 13 and 20% in the standard of care arm and a coefficient of variation of 0.25, we will have at least 80% power to detect a 40% reduction in the intervention arm.

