Analysis will be conducted at cluster-level due to the small number of clusters [16]. For each cluster the proportion of participants with ≥80% adherence is measured and the log(proportion) compared by study arm using a t test. We will also conduct an adjusted analysis for the intervention effect, adjusting for imbalances of individual-level variables at baseline, using a two-stage approach [16]. We will fit a logistic regression model at the individual-level including any baseline variable which look imbalanced by study arm and variables which we anticipate to be associated with poor adherence. The expected outcome for each individual is calculated and summed at the cluster-level. The log of cluster-level residual (expected number of outcomes with the observed number of outcomes) is compared by study arm using a t test. We plan to also specify a limited number of subgroups and endpoint(s) they relate to. Subgroups will be measured at the cluster-level (e.g. province) or individual-level (e.g. sex, education, stigma-level). We will then estimate the intervention effect in each subgroup. A full statistical analysis plan will be developed before study completion.

For the secondary objectives, we will generate a binary variable indicating whether enrolled participants had successfully completed six months of TB treatment or not. Unfavourable outcomes will be measured by generating a binary variable indicating whether enrolled participants had an unfavourable outcome 18 months after enrolment.

A detailed statistical analysis plan will be written prior to any analyses. The trial investigators will have access to the final dataset.

For the qualitative component, audio-recordings and process notes will be transcribed and where necessary translated prior to analysis. Data will be analysed using QSR NVIVO 10 qualitative analysis software and manual reviewing. Thematic analysis using deductive and inductive approaches will be used to describe the themes. A codebook will be created using the deductive themes and updated with any new themes that develop from the transcripts. Saturation of themes will be assessed during study implementation by frequent review of the transcripts. For reliability, the original transcript and codebook will be sent to two independent reviewers.

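### The 90% power stated for the primary endpoint does not follow from its printed inputs: a CV of 0.12 gives about 99.9% on the non-adherence scale or about 69% on the adherence scale

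*Protocol article*

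**What the plan says.** Sample size considerations in the protocol article gives the inputs shared by all endpoints. The cluster size is fixed by "Throughout we have assumed a harmonic mean of 145 TB patients/cluster", with nine clusters per arm and a two-sided 5% type I error.

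The primary-endpoint calculation is headed as the proportion above 80% adherence but starts from a "percentage with non-adherence in the standard of care arm of 30% and coefficient of variation of variation of 0.12, we will have 90% power". The power claim in full is "we will have 90% power to detect a 40% reduction in the endpoint in the intervention arm". A 40% reduction takes non-adherence from 30% to 18%, which is the same as adherence rising from 70% to 82%.

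Data management and analyses then sets the primary test on the adherence side: "For each cluster the proportion of participants with ≥80% adherence is measured and the log(proportion) compared by study arm using a t test".

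**The concern.** A between-cluster CV is relative to its own proportion, so 0.12 implies very different spreads on the two scales. In the standard of care arm it is an SD of 0.12 × 0.30 = 0.036 if it refers to non-adherence, and 0.12 × 0.70 = 0.084 if it refers to adherence. The text names neither. It gives a non-adherence rate, calls the effect a reduction in the endpoint, and defines and tests the endpoint as adherence, which the intervention is meant to raise.

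Power for the primary endpoint is the main design property. If 0.12 is on the adherence scale, a null result would be read as stronger evidence against a 12-point gain than the design can supply. If it is on the non-adherence scale, the trial can detect a much smaller effect than the one stated.

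**Working it through.** **Inputs** (all from Sample size considerations): c = 9 clusters per arm, m = 145, two-sided 5%, p0 = 0.30 and p1 = 0.30 × 0.60 = 0.18 non-adherent (0.70 and 0.82 adherent), k = 0.12. The stated power is 90%.

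**Formula** (standard unmatched cluster formula for proportions, CV form):

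c = 1 + (z_α/2 + z_β)² × V / (p0 − p1)², with V = p0(1−p0)/m + p1(1−p1)/m + k²(p0² + p1²).

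Solved for power: z_β = √[(c − 1)(p0 − p1)² / V] − 1.96.

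**Does the formula match the article's other claims?**

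| Endpoint | Inputs | Computed | Stated |
|---|---|---|---|
| Treatment success | 0.80 to 0.90, k = 0.06 | 92.4% | 90% |
| Unfavourable outcome, low end | 0.13 to 0.078, k = 0.25 | 80.6% | at least 80% |
| Unfavourable outcome, high end | 0.20 to 0.12, k = 0.25 | 87.9% | at least 80% |

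It agrees with the unfavourable-outcome claim and comes within 2.4 points for treatment success.

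**Primary endpoint.** The binomial part of V is the same on both scales: (0.30 × 0.70 + 0.18 × 0.82)/145 = 0.00247.

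- *k on non-adherence.* Between-cluster part: 0.0144 × (0.09 + 0.0324) = 0.00176, so V = 0.00423. z_β = √(8 × 0.0144/0.00423) − 1.96 = 5.22 − 1.96 = 3.26. **Power 99.9%**. Clusters per arm for 90%: 1 + 3.2416² × 0.00423/0.0144 = 4.1.
- *k on adherence.* Between-cluster part: 0.0144 × (0.49 + 0.6724) = 0.01674, so V = 0.01921. z_β = √(8 × 0.0144/0.01921) − 1.96 = 2.45 − 1.96 = 0.49. **Power 69%**. Clusters per arm for 90%: 1 + 3.2416² × 0.01921/0.0144 = 15.0.

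**What would give 90%?**

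- Keeping the effect, k must be about 0.26 on non-adherence or about 0.086 on adherence.
- Keeping k = 0.12 on non-adherence, 90% is reached at 30% to 22.2%, a 26% reduction.
- Keeping k = 0.12 on adherence, 90% is reached only at 70% to 86.2%. Non-adherence then falls from 30% to 13.8%, a 54% reduction.

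**Sensitivity.**

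| Variant | k on adherence | k on non-adherence |
|---|---|---|
| Noncentral t, 16 df | 68.4% | 99.9% |
| t test on the log scale | 68.6% | 99.9% |
| Formula without the +1 cluster | 73.8% | above 99.9% |
| Same between-cluster SD in both arms | 75.1% | 99.8% |
| One-sided 5% | 78.9% | above 99.9% |
| Cluster size 100 to 200 | 66% to 70% | 99.6% to 99.99% |
| Simulated t test on log proportions | about 65% | above 99.9% |

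Reading 0.12 as an intracluster correlation gives about 39%, and as an absolute SD about 48%. No variant that uses 0.12 as a CV on one scale in both arms comes within 2 points of 90%.

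**The case against.** The strongest reply is a third reading. Suppose 0.12 is the CV of adherence in the standard of care arm (SD 0.084), and the calculation was done on non-adherence after conversion: k = 0.084/0.30 = 0.28 in both arms. Power is then 87.1% by the formula above, 88.9% by a t test on the log scale and 90.6% without the +1. If 0.12 was rounded up from 0.115, the first two become 89.2% and 90.7%. On this view true power is in the high 80s and the fault is mainly one of labelling.

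This may be how the figure arose, but it does not rescue the text. The article prints neither 0.28 nor a conversion. The same step applied to treatment success in the same paragraph (CV 0.06 × 0.80/0.20 = 0.24 on non-success, 20% to 10%) gives 98.6% against a stated 90%. Using 0.06 directly gives 92.4%. The paragraph would therefore have to treat its CVs in two different ways.

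Three further points have weight. The 69% assumes a constant CV in both arms, so that the between-clinic SD rises from 0.084 to 0.098; with a constant SD it is 75%. If 0.12 does belong to non-adherence, the trial is amply powered and the error is harmless to it. And since 30% to 18% and 70% to 82% are the same 12-point difference, calling it a reduction in the endpoint is loose wording, not a different hypothesis.

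**Conclusion.** The concern holds. With the printed inputs, power is 99.9% if the CV of 0.12 refers to non-adherence and about 69% if it refers to adherence. The stated 90% is about 10 points too low in the first case and about 21 points too high in the second. The article does not show which applies, so the true design power cannot be settled from it.

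The figures assume the standard CV formula with equal CVs in the two arms. They are not sensitive to cluster size or to the choice of normal or t approximation, and every variant on the adherence scale stays below 80%. The adverse case is the one where the CV belongs to the tested proportion. The chance of missing a true rise from 70% to 82% is then about 31% instead of 10%.

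**What to change.** Say which proportion the CV of 0.12 describes, and correct the figure that is wrong:

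- **CV of the proportion adherent:** restate power as about 69% for 70% versus 82%, or give 70% versus about 86% as the difference detectable with 90% power.
- **CV of the proportion non-adherent, 0.12 intended:** restate power as above 99%, or give 30% versus about 22% as the difference detectable with 90% power.
- **CV of the proportion non-adherent, another value intended:** replace 0.12 by the value used. About 0.26 would give 90%, and it is close to the 0.25 used for unfavourable outcome.
- **CV converted between scales:** print the converted value and the resulting power.

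In each case, also give the effect on the scale that is tested, as a ratio of adherent proportions: 0.82/0.70 = 1.17.

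The cost is the wording of one paragraph. Recruitment and the analysis do not change, although the stated power may become less favourable.

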### Data management and analyses

Research staff were trained to capture all data into web-based database which is encrypted to ensure compliance to the South Africa’s Protection of Personal Information Act (POPI). If Internet connection is not available, a paper-based system is implemented and data captured into the web-based system once Internet connectivity is restored. Documents containing personal identifiers will be kept in lockable cabinets that are only accessible by study staff.

The database access is restricted with an encrypted password. All fields have automated system checks, which verify missing, range, and future dates. Any personal identifiers will be removed from the analytic dataset prior to the data analysis phase of the study. The data management team carries out a centralised statistical monitoring. Baseline characteristics data will summarised at individual level for all participants in the two arms. The individual data will include age, gender, ethnicity, education, marital status, number of people they live with, special risk factors for TB, TB history, HIV status, antiretroviral status, CD4 count, and viral load. We will also report on TB treatment category, sputum results, smoking, alcohol and recreational drugs use, and TB related stigma at three time points which are at the start of taking TB treatment, completion of TB treatment, and end of 18 months follow-up. The study is also collecting data on social harm during the course of treatment at the end of TB treatment and adverse events will be reported to the Ethics committees. To answer our main objective, we will measure adherence using data from the medication monitors. A box opening any time during the day will be taken as a proxy for medication intake. Adherence will be calculated by dividing the number of days when pills were taken over number of days that pills were supposed to be taken to generate an adherence proportion for each individual enrolled. We will then generate a binary variable for each participant based on ≥ 80% adherence.

Analysis will be conducted at cluster-level due to the small number of clusters [16]. For each cluster the proportion of participants with ≥80% adherence is measured and the log(proportion) compared by study arm using a t test. We will also conduct an adjusted analysis for the intervention effect, adjusting for imbalances of individual-level variables at baseline, using a two-stage approach [16]. We will fit a logistic regression model at the individual-level including any baseline variable which look imbalanced by study arm and variables which we anticipate to be associated with poor adherence. The expected outcome for each individual is calculated and summed at the cluster-level. The log of cluster-level residual (expected number of outcomes with the observed number of outcomes) is compared by study arm using a t test. We plan to also specify a limited number of subgroups and endpoint(s) they relate to. Subgroups will be measured at the cluster-level (e.g. province) or individual-level (e.g. sex, education, stigma-level). We will then estimate the intervention effect in each subgroup. A full statistical analysis plan will be developed before study completion.

For the secondary objectives, we will generate a binary variable indicating whether enrolled participants had successfully completed six months of TB treatment or not. Unfavourable outcomes will be measured by generating a binary variable indicating whether enrolled participants had an unfavourable outcome 18 months after enrolment.

A detailed statistical analysis plan will be written prior to any analyses. The trial investigators will have access to the final dataset.

For the qualitative component, audio-recordings and process notes will be transcribed and where necessary translated prior to analysis. Data will be analysed using QSR NVIVO 10 qualitative analysis software and manual reviewing. Thematic analysis using deductive and inductive approaches will be used to describe the themes. A codebook will be created using the deductive themes and updated with any new themes that develop from the transcripts. Saturation of themes will be assessed during study implementation by frequent review of the transcripts. For reliability, the original transcript and codebook will be sent to two independent reviewers.

For economics evaluation, all time and motion data will be collected onto a paper form and captured onto an Excel workbook by trained research assistants. The health economist will review the data on a regular basis and clarifications requests made promptly to avoid recall bias. Patient costing data will be collected on case report forms and entered into a password-protected database created in REDCap database. Data will be exported from REDCap into STATA (version 14, StataCorp LP, College Station, Texas) for analysis.

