### Description of study arms and procedures

#### Intervention clinics

Enrolled patients receive the differentiated care adherence package. This includes standard patient education and provision of medication monitor programmed to alert patients (using sound and a light on the box) on a daily basis as a reminder to take their medication (Table 1). Patients are educated on how to use the medication monitor by the study team. The medication monitor transmits a daily signal to the Wisepill system (system), referred to as heartbeat, to indicate that it is working properly. There are also additional reminders for monthly dispensing visits and the device uploads data in real-time to a central database that allows for weekly review by research staff. Weekly automated reports are generated from the system that lists patients who had missed any doses and those whose devices are not sending a signal correctly. A step-wise approach to missed doses is then implemented that includes phone calls, home visits, and motivational counselling for those who consistently miss medication doses (Table 2). Automated SMS reminders are sent to any patient in the intervention with a missed dose. A second or third missed dose in a week triggers a research staff-initiated phone call to the patient, and four or more missed doses in a week trigger a home visit. Phone calls and home visits are scripted. Should four or more doses be repeatedly missed, additional adherence measures such as motivational counselling is done. When participants visit the clinic for their usual dispensing visit, the research staff shows the participant their own data and discusses their medication adherence history.

**Table 1 Tab1:** Description of scheduled study visits

***Study Visit*** ***Month (M) and*** ***Day (D)***	***D0*** ***(Enrolment)***	M1	M2	M3	M4	M5	M6	M9	M12	M15	M18
Informed consent	**√**										
Eligibility criteria verified	**√**										
Of those eligible:											
Locator information	**√**	**√**	**√**	**√**	**√**	**√**	**√**	**√**	**√**	**√**	**√**
Brief medical history	**√**										
Risk assessment for TB	**√**										
Economics questions	**√**										
Stigma scale	**√**						**√**				**√**
Facility dispensed treatment	**√**	**√**	**√**	**√**	**√**	**√**					
Education on the medication monitor and monitor provided to patient	**√**										
Medication monitor configured to have visual and audio reminders—intervention arm only	**√**										

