#### Standard of care clinics

Enrolled patients are provided with a return date for collection of repeat medication in 30 days. Patients are also provided with the medication monitor and educated on its use by the study team (Table 1). The medication monitor records data on box opening and is not configured to have visual or audio reminders for intakes or refills. The medication monitor transmits a daily “heartbeat” signal to the system to indicate that it is working properly. In contrast to the intervention clinic patients, data collected on the system is not reviewed during follow-up study visits. Patients receive counselling regarding their TB treatment as per standard of care only. Neither the research staff nor the patient accesses the medication monitor information at follow-up study visits.

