### Trial outcomes

The primary study endpoint is medication adherence which will be measured as the proportion of patients by arm with >80% adherence, as measured by the medication monitor. For those lost to follow-up during treatment, we will assume no drug intake (100% non-adherence) for the period from the date of being lost to follow-up to the date of scheduled treatment completion. Secondary endpoints will be successful outcome at the end of treatment and unfavourable outcomes at 18 months post enrolment. Treatment success will be measured as the proportion of patients by arm that either have a documented cure or treatment completion by 210 days following commencement of TB treatment. A TB culture will be performed at the end of treatment to confirm response to treatment. TB recurrence will be determined through incident TB cases in the year following completion of DS-TB treatment. Unfavourable outcome at 18 months after enrolment will include on-treatment lost to follow up, death, treatment failure, and treatment recurrence. Fidelity of the intervention will be measured by reporting on percentage of patients who were supposed to receive an SMS or phone call who did and percentage of patients who received counselling when required. We will also report on percentage of boxes with failures. We will also report on percentage of patients withdrawing from study due to refusal of using digital adherence technology.

Qualitative outcomes will be on appropriateness and perceptions of patients as well as providers involved with the implementation of the intervention. We will also report on reaction to use of the medication monitor as well as the suitability of this medication monitor to participant living conditions, the motivators of using the medication monitor to take treatment, and challenges to integrating the differentiated model of care into the current health system. We will further explore differences across patients by age, category of adherence, and location.

Economic outcomes will be based on cost per person with >80% adherence to DS-TB treatment, cost per person with TB who successfully completed DS-TB treatment, proportion experiencing catastrophic costs, and cost drivers and incremental cost-effectiveness ratio.

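### The adherence ratio does not separate device failure from missed doses, and fault detection is described for intervention clinics only, so the primary comparison can be biased towards the intervention

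*Protocol article*

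**What the plan says.** **Endpoint.** Under *Data management and analyses* the protocol article says "A box opening any time during the day will be taken as a proxy for medication intake" and then "Adherence will be calculated by dividing the number of days when pills were taken over number of days that pills were supposed to be taken". The ratio is cut into a yes/no outcome: "We will then generate a binary variable for each participant based on ≥ 80% adherence" (*Trial outcomes* words the cut-off as strictly above 80%). The only special rule is in *Trial outcomes*: after loss to follow-up, no intake is assumed until scheduled treatment completion. Nothing is said about days on which the device failed.

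**Intervention arm.** *Intervention clinics* describes a weekly report that "lists patients who had missed any doses and those whose devices are not sending a signal correctly". Apparent missed doses lead to an SMS, a call or a home visit, and staff go through the monitor data with the patient at dispensing visits. The Discussion ties the weekly reports to delivery of differentiated care.

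**Control arm.** *Standard of care clinics* describes the same daily heartbeat but no fault list, and adds: "In contrast to the intervention clinic patients, data collected on the system is not reviewed during follow-up study visits".

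**Both arms.** *Trial outcomes* promises: "We will also report on percentage of boxes with failures". The Discussion says that lost monitors will be replaced. Neither statement is limited to one arm.

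**The concern.** The device is both part of the intervention and the instrument that measures the primary outcome. If it stops capturing openings, the stated ratio cannot tell a broken monitor from an untaken dose.

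That alone would add error to both arms. The concern is that the routes by which a fault would come to light (the weekly list, contact after an apparent missed dose, data review at dispensing visits) are described for one arm. A fault that persists longer in control clinics would pull control adherence down, and the intervention would look better with identical pill-taking. The direction is predictable and lies in the primary comparison. Reporting the percentage of boxes with failures would describe the problem without correcting the endpoint.

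**Working it through.** **1. What the stated rule does.** Let a course have D due days, of which x are lost to device failure with no opening captured. With true adherence *a*, unrelated to the failure, the ratio gives

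observed adherence = a × (D − x) / D.

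A patient who took every dose of 180 with 40 days lost scores 140/180 = 77.8% and is classed non-adherent. With the lost days removed from both parts, the score is 140/140 = 100%.

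**2. How many lost days matter.** Taking six months of treatment as D = 180 (my assumption), a patient falls below 80% when x > 180 × (1 − 0.80/a).

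| True adherence | Lost days that take the patient below 80% |
|---|---|
| 100% | more than 36.0 |
| 95% | more than 28.4 |
| 90% | more than 20.0 |
| 85% | more than 10.6 |

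**3. Yardstick from the plan.** *Sample size considerations* assumes 30% non-adherence in control and a 40% reduction: 0.30 × 0.40 = 12 points, to 18%. In adherence terms this is 70% to 82%.

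**4. Spurious difference with no true effect.** The documents give no outage rate, so the rates here are assumptions. True adherence is 70% in both arms. A share f of adherent patients has an outage long enough to drop below the cut-off. Observed adherent share = 0.70 × (1 − f).

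| f control / intervention | Observed control | Observed intervention | Difference | Ratio | Share of 12 points |
|---|---|---|---|---|---|
| 5% / 1% | 66.5% | 69.3% | 2.8 | 1.04 | 23% |
| 10% / 2% | 63.0% | 68.6% | 5.6 | 1.09 | 47% |
| 15% / 3% | 59.5% | 67.9% | 8.4 | 1.14 | 70% |

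**5. Effect on the false-positive rate.** I used 9 clusters per arm, m = 145, two-sided 5%, and k = 0.12, all from *Sample size considerations*. The variance is

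v = p0(1 − p0)/m + p1(1 − p1)/m + k²(p0² + p1²),

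with noncentrality |p0 − p1| / √(v/9) and a t test on 16 degrees of freedom. This works on the proportion scale; the plan tests log proportions, so the results are approximate.

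The article's 90% power for this endpoint does not tell us which scale k belongs to. The same variance in the usual cluster formula (9 − 1 clusters) gives 99.9% if k applies to non-adherence and 69% if it applies to adherence. That mismatch is a separate matter; I show both readings.

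For the 10% / 2% row:
- k on adherence: v = 0.00161 + 0.00149 + 0.01249 = 0.01559; √(v/9) = 0.0416; noncentrality 0.056/0.0416 = 1.35; chance of a significant result 24%.
- k on non-adherence (0.37 against 0.314): v = 0.00161 + 0.00149 + 0.00339 = 0.00648 before rounding of the parts; √(v/9) = 0.0268; noncentrality 2.09; chance 50%.

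With misclassification in control only:

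| f in control, none in intervention | k on adherence | k on non-adherence |
|---|---|---|
| 2% | 6% | 8% |
| 5% | 12% | 25% |
| 10% | 35% | 70% |
| 15% | 67% | 95% |

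With equal failure (5% / 5% or 10% / 10%) the rate stays at 5% under both readings. The arm difference drives the result, not failure as such.

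**The case against.** A reader might infer that the plan declares silent days to be missed doses, that faults are repaired in one arm only, and that the result is therefore biased. The documents do not support that much.

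- **Not transmitting is not the same as not recording.** The article describes recording of openings and sending of the heartbeat separately and does not say whether openings during signal loss are stored and uploaded later. A silent day is lost only if the opening is lost too.
- **The restriction to one arm is inferred from where the text sits.** *Standard of care clinics* rules out review and access at follow-up study visits. It does not rule out remote checks of device function. Centralised statistical monitoring, reporting of box failures and replacement of lost monitors carry no arm restriction.
- **No repair action or repair time is stated for either arm.** The intervention report covers "those whose devices are not sending a signal correctly", but the stepwise response that follows is for missed doses. Study contacts are monthly during treatment in both arms.
- **Handling of invalid monitor days may sit in the full protocol or the statistical analysis plan**, which are not shown.

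The first three points stand, and they turn a claim of bias into one of possible bias. The last stands only in part. The article states the ratio for the primary endpoint, so a later plan that applies it as written carries the problem forward. The difference in fault detection is trial conduct described here, not analysis detail left for later.

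**Conclusion.** The point holds as a risk, not as a demonstrated bias. Read as written, the ratio scores days lost to device failure as non-adherence, and detection of such failure is described for intervention clinics only. Together these can misclassify patients differentially, in the intervention's favour.

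The size is unknown. The 2.8 to 8.4 points rest on assumed outage rates, a fivefold difference between arms, true adherence of 70% in both, and outages long enough to reclassify every affected adherent patient. If failures are rare, short, recovered by later upload, or equal between arms, the effect is small or absent. It still deserves correction before analysis: it concerns the primary endpoint, its direction is predictable, and the heartbeat data needed are transmitted in both arms.

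**What to change.** 1. **Primary analysis.** Define a device-down day identically in both arms from the stored heartbeat log: no heartbeat, and no opening recorded or later uploaded for that day. Remove such days from numerator and denominator.
2. **Loss to follow-up.** Keep the rule in *Trial outcomes* unchanged, including its start date. Days after that date still count as missed, whatever the device status.
3. **Sensitivity analysis.** Repeat with device-down days counted as missed, because a silent device may also mean that the patient has disengaged.
4. **Reporting.** Give device-down days by arm alongside the planned percentage of boxes with failures.
5. **Conduct.** For any patients still on treatment, apply the same heartbeat-only fault check in both arms without revealing dosing data. *Trial status* has recruitment running to December 2020 and the article appeared in June 2021, so this may reach few patients. The analysis rule does not depend on it.

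**Cost.** A paragraph of analysis wording, use of data already transmitted, and at most one extra device list for control clinics. The downside is that excluded days are assumed to resemble monitored days, which is generous to a patient who abandons the device before being declared lost. A fault check in control clinics also adds slight contact there.
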